### Sample Size

Sample size was calculated based on the 2 primary outcomes using the following assumptions: (1) a cluster size of 77 women and 140 antenatal contacts in the randomized health facilities for a 21-month enrollment period; (2) a 20% coverage of timely antenatal care visits and 12% of women screened and managed for hypertension in the control group, based on data from the 2014 Demographic and Health Survey; and (3) an a priori intracluster correlation coefficient of 0.1, commonly reported for such process outcomes [20]. The given sample size will have more than 80% power to detect a minimum clinically significant change from 20% to 33% for timely antenatal care visits and from 12% to 22% for hypertension screening and management. The sample size was calculated using Stata 16 (StataCorp).

### Recruitment

Both the intervention and control health facilities received the same number of initial training sessions. The initial training duration was decided based on the underlying skill level of the health workers and the complexity of the tasks within the eRegistry. In total, 276 health workers (102 family welfare assistants, 71 health assistants, 44 community health care providers, 20 family welfare visitors, 20 family planning inspectors, and 10 assistant health inspectors) were trained over 21 sessions in using the eRegistry. Retraining was provided to health workers in both the intervention and control arms at regular intervals of 3-6 months and over 36 sessions during the trial.

### Allocation

#### Randomization of Health Facilities

The unit of randomization was a health facility (community clinics or family welfare clinics) located in the study area, which provided antenatal, childbirth, and postpartum care. We performed stratified restricted randomization with a 1:1 ratio. The randomization was stratified based on the type of clinic (family welfare clinics and community clinics) and whether the facility was staffed with a care provider. The randomization within each stratum was then restricted based on (1) the clinic’s allocation as intervention or control within a preceding project in the study area for strengthening maternal and child health services; (2) the technological skills of the staff; (3) the monthly number of clients attending the clinic; and (4) the monthly number of antenatal care visits. To measure the technological skills of the staff, we created an index using information from a provider and a clinic survey conducted by the study team in preparation for the trial. The index included items such as health workers’ technological capabilities, such as the use of phones for SMS and internet, and their comfort using technology. Statisticians at the Centre for Intervention Science in Maternal and Child Health (CISMAC), University of Bergen, undertook randomization.

#### Individual Women Within the Trial

The family welfare assistant enrolled individual women in the trial at pregnancy identification and registration. At that time, women were required to provide informed consent to receive communication from the study team and a home visit 8-14 days after the birth of the child (Figure 2). Women were then asked about their preferred public health facility for antenatal care, which determined allocation to an intervention or control cluster (Figure 3). Women may also be first identified as pregnant at a health facility. At this contact, women were registered in the eRegistry and automatically assigned to an intervention or control cluster based on the allocation status of that health facility (Figure 3). After completion of the pregnancy, the data collection team conducted a postpartum home visit within 8-14 days of birth for collection of outcome data.

**Figure 3 figure3:**
[figure not shown]
Identification and enrollment of individual pregnant women in the trial. eRegistry: electronic registry.

### Blinding

Due to the nature of the intervention, it was not possible to blind facility-based health workers to the allocation. Community-based health workers registering and allocating pregnant women were blinded to the allocation status of their preferred health facility. The data collectors conducting the postpartum home interviews were blinded to the allocation of individual women. Researchers performing the final analyses will be blinded to group allocation.

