**Health worker: community**					
	Digital client health records	FWA, HA		✓	✓
	Client identification (biometric and palm-based) and registration	FWA, HA		✓	✓
	Feedback dashboards	FWA, HA			✓

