#### Intervention Arm

In the intervention arm, the eRegistry supported 3 data-driven DHIs linked to the digital client health records (Table 1) as follows: (1) for facility-based staff, health worker clinical decision support based on national guidelines to promote the correct management of health conditions identified in antenatal care; (2) for both field- and facility-based staff, feedback dashboards tracking the health worker’s progress toward pregnancy registration, antenatal care attendance and utilization, and clinical screening and management targets; and (3) for pregnant women, targeted client communication in the form of SMS text messages to address gaps in the timely attendance of antenatal care visits and facility delivery. Following the initial implementation of the eRegistry, the DHIs in the intervention arm were gradually introduced over the course of the trial; health worker clinical decision support was introduced in October 2018; targeted client communication via SMS and feedback dashboards were implemented in June 2019. Digital client health records were accessible across the cadres of health workers, facilities, and arms of the health system for a comprehensive longitudinal tracking of clients’ health status and services received (Table 1).

Guideline-based clinical decision support and feedback dashboards were developed in close collaboration with health workers. The decision support comprised referral and counseling reminders, medication alerts, and scheduling based on the recommended guidelines in the public health system. Feedback dashboards were customized for each cadre of health workers, with indicators of antenatal care attendance and screening and management of gestational diabetes, hypertension, and anemia. Targeted client communication included SMS text message reminders of routine antenatal care, referral facilitation SMS text messages for those at risk, and facility delivery reminders for those who are advised to have an institutional delivery. All DHIs were triggered by data entry into the eRegistry at the point of care by the health workers.

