### Outcomes

The outcomes were formulated based on their relevance to the health system context and were meant to capture the potential effects of the specific DHIs under assessment. Data for the primary (Table 2) and secondary outcomes (Table 3) will be derived from the eRegistry’s client health records and through postpartum home visit interviews.

**Table 2 table2:** Primary outcomes, data sources, and definitions.

Primary outcome	Sources of data	Measurement sequence	Definition	Intervention subcomponents with most direct effect
Timely attendance at eligible ANC^a^ visits	Postpartum household survey	Registrations continuously at point of care Household visit after the completion of pregnancy	Proportion with timely attendance	Targeted Client Communication via SMS text message: ANC appointment reminders
Screening and management for hypertension in pregnancy	Case records from the eRegistry^b^	Registrations continuously at point of care	Proportion that has at least one ANC at a randomized health facility with: Blood pressure measurement at routine ANC visits, and Referred if blood pressure is high, or Referred if blood pressure is high outside of the routine ANC visit	Health worker clinical decision support Feedback dashboards with action items

^a^ANC: antenatal care.

^b^eRegistry: electronic registry.

**Table 3 table3:** Secondary outcomes, data sources and definitions.

Secondary outcome	Sources of data	Measurement sequence	Definition	Intervention subcomponents with assumed direct effect
Timely first ANC^a^ visit	Case records from the eRegistry^b^ Postpartum household survey	Registrations continuously at point of care Household visit after the completion of pregnancy	Proportion of women that have an ANC visit at or before 16 weeks among those with a home pregnancy registration before 16 weeks	Targeted Client Communication via SMS text message: ANC appointment reminders
High-risk women successfully referred to a skilled provider for additional care	Case records from the eRegistry Postpartum household survey	Registrations continuously at point of care Household visit after the completion of pregnancy	Proportion of women that received additional care during pregnancy among those that are referred for severe anemia, or hypertension or diabetes during pregnancy	Health worker clinical decision support Targeted client communication via SMS: Referral reminders, high risk, facility delivery reminders

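### The blinding claim for community enrolment is not credible as stated once intervention-arm field staff have dashboards tracking pregnancy registration, so recruitment may differ by arm with only weak analytic protection

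*Protocol article*

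**What the plan says.** On blinding, the protocol article says: "Community-based health workers registering and allocating pregnant women were blinded to the allocation status of their preferred health facility". The same section names only facility-based workers as impossible to blind.

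On who enrols, the section on individual women says: "The family welfare assistant enrolled individual women in the trial at pregnancy identification and registration". The woman's stated preferred facility then fixes her arm. There is a second route for women first identified as pregnant at a clinic: "women were registered in the eRegistry and automatically assigned to an intervention or control cluster based on the allocation status of that health facility".

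On the intervention, the Intervention Arm section describes: "for both field- and facility-based staff, feedback dashboards tracking the health worker’s progress toward pregnancy registration". Table 1 has a row "Feedback dashboards" for family welfare assistants and health assistants that is ticked in one column only. Read with the Intervention Arm section, that column is the intervention arm. The dashboards started in June 2019. The analysis takes women enrolled from October 2018 to June 2020.

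On the outcome most exposed, Table 3 defines timely first antenatal visit "among those with a home pregnancy registration before 16 weeks".

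On the analysis, Statistical Methods presents women's age, parity, socioeconomic status and education. It adjusts for confounders in the primary analysis only when adding them changes the effect measure by more than 5%.

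**The concern.** Clusters were randomised first and women entered afterwards, so the comparison depends on enrolment working the same way in both arms. The blinding sentence is what assures the reader of that for home registration. The cadre that does the enrolling, however, is given an arm-specific tool, and one of the things that tool tracks is enrolment itself. A worker with a registration target may find more women, or find them earlier, or reach women who would otherwise have stayed outside the system. For clinic registration there is no blinding at all.

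If that happens, the arms can differ in the number, gestation and care-seeking habits of enrolled women for reasons unrelated to the care they received. Timely first antenatal visit is the most directly exposed outcome, because its denominator is made by early home registration.

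**Working it through.** **1. Do the passages fit together?**

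- Enroller at home: the family welfare assistant.
- Cadres with a community dashboard: family welfare assistants and health assistants, intervention arm only.
- Content of the dashboard: pregnancy registration among its targets.
- Blinding section: community workers who register and allocate are blinded to the preferred facility's status.

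A dashboard reveals the worker's own arm. The blinding sentence concerns the facility the woman chooses. The conflict is therefore practical rather than word for word, and the article does not say how community workers are tied to arms.

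**2. Were non-facility workers allocated to arms?** Under Cluster Level, 59 + 64 = 123 health workers were allocated. Under Recruitment, the trained facility staff number 44 + 20 = 64. So at least 123 − 64 = 59 allocated workers come from other cadres, if the allocated facility staff are among those trained. The itemised training list sums to 102 + 71 + 44 + 20 + 20 + 10 = 267 against a stated 276. If all 9 unlisted workers were facility staff, the minimum is still 59 − 9 = 50. The other cadres include 20 + 10 = 30 supervisory inspectors. Even if all 30 were allocated, at least 50 − 30 = 20 would be family welfare or health assistants.

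**3. How much enrolment is exposed?** June 2019 to June 2020 is 13 months (12 if the start was late in June): 13/21 = 61.9%, or 12/21 = 57.1%. The household survey, which is the source for timely attendance, also began in June 2019 and covers a subset of registered pregnancies. The exposed share among surveyed women may therefore be higher.

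**4. The plan's own power figure.** Inputs: 30 and 29 clusters, intracluster correlation 0.1, cluster size m = 77 or 140, two-sided alpha 0.05 (assumed, as it is not stated). Effective n per arm = clusters × m / [1 + (m − 1) × 0.1].

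| Outcome | m = 77 | m = 140 |
|---|---|---|
| Timely visits, 20% vs 33% | 92.5% | 93.6% |
| Hypertension, 12% vs 22% | 86.6% | 88.2% |

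The lowest value over the method variants tried is 86.0%. The claim of more than 80% holds and this point does not touch it.

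**5. Illustration of size.** Assume no true effect, so both arms would show the control rate of 20%. Assume dashboards add 10% more registrations while they run, and that the added women attend on time at rate q. These are assumptions; the documents give no such figures.

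- Added weight: w = 0.10 × 13/21 = 0.062
- Apparent rate: (0.20 + w × q) / (1 + w)
- q = 0.10: (0.20 + 0.062 × 0.10) / 1.062 = 19.4%
- q = 0.50: (0.20 + 0.062 × 0.50) / 1.062 = 21.7%

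The shift is −0.6 to +1.7 percentage points, an apparent risk ratio of about 0.97 to 1.09. With 10% extra over the whole enrolment period the range is (0.20 + 0.01)/1.10 = 19.1% to (0.20 + 0.05)/1.10 = 22.7%. With 30% extra over 13/21 and q from 5% to 40%, the apparent risk ratio is 0.88 to 1.16.

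For scale, the standard error of the arm difference at 20% is about 3.4 to 3.5 points, so +1.7 points is about half a standard error.

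**6. Would the 5% rule catch it?** At the lower end (0.97), moving the estimate back to 1.00 is a change of about 3%, so the rule would not trigger even if the covariates explained all of it. At the upper end (1.09) the change is about 8%, so it would trigger only if measured covariates removed most of the bias.

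**The case against.** The best defence has four parts.

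First, a reader might infer that intervention-arm community workers cannot have been blind from June 2019. The text does not establish that. Allocation follows the woman's stated preference, and one worker's women might prefer facilities in both arms. Also, 102 + 71 = 173 family welfare and health assistants were trained while only 123 workers of all cadres were allocated, so at least 50 of them are not counted as allocated and who held a dashboard is unclear. This stands. It limits the finding to a claim that is not credible as stated, and does not show that blinding was broken.

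Second, a reader might infer that the analysis offers no protection. It does: background characteristics are presented, and there is a conditional adjustment rule. This stands too, but the rule depends on the data and does not address who was registered or when. A fuller covariate list may sit in an analysis plan that is not shown; the 5% rule itself is fixed in the article.

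Third, clinic staff have no discretion over the arm, because assignment is automatic, and the eligibility section asks that every identified pregnancy be entered. That answers manipulation of assignment. It does not answer differences in who is found, who consents to the home visit, or when. Nor can one infer that clinic-identified women were never asked the allocation question: the article describes no such step for them, but the enrolment figure is not available here.

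Fourth, gestational age and place of registration look like natural covariates. If the intervention changes when and where women register, they are consequences of it, and adjusting for them could remove part of the effect or add bias. This stands and shapes the fix. An analysis confined to home-registered women has a similar weakness, since it keeps the group whose enrolment the community dashboards target.

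**Conclusion.** The concern holds in limited form. For the dashboard period, about 13 of 21 enrolment months, the blinding statement for community workers is not credible as written, and it never covered clinic registration. Differential recruitment by arm after randomisation is possible, and timely first antenatal visit is the outcome most directly at risk. The planned protection is weak.

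Direction and size are unknown. Under the stated assumptions a null effect of 20% would appear as about 19.4% to 21.7%. That is small beside the 13-point difference the trial is sized for, but a ratio estimate could move by −3% to +9%. It would be wrong to start such an illustration from 33%: that is the rate under the full target effect, so it cannot represent no change in care. The documents do not show that recruitment differed, only that it could have and that the plan would not clearly reveal it.

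**What to change.** - Reconcile the Blinding section with the Intervention Arm section, Table 1 and the section on individual women. Say how community workers are tied to arms and who held dashboards. Qualify the blinding statement for the period from June 2019 and state that clinic registration was not blinded.
- Replace the 5% change rule with fixed adjustment in the primary model for maternal age, parity and education. The intervention cannot alter these in an individual woman, and they are already collected. This deals with measured differences only.
- Report registrations per clinic, gestational age at registration and place of registration (home or clinic) by arm, before and after June 2019.
- State the recruitment-bias risk for timely first antenatal visit wherever that outcome is defined and reported.
- Keep gestational age and place of registration out of the primary model. Use them only in labelled sensitivity analyses, and add one by enrolment period.

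The cost is a few model degrees of freedom, some descriptive tables from data already held, and a less favourable blinding statement.

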### Intervention

#### Overview

An eRegistry was implemented in the study area by the International Centre for Diarrhoeal Disease Research, Bangladesh (icddr, b), in collaboration with the Norwegian Institute of Public Health, the University of Oslo, and the Ministry of Health and Family Welfare in Bangladesh. Health workers in both the intervention and control arms document clinical information in the eRegistry’s digital client health records at the point of care. Health workers’ cadres under both the Directorate General of Health Services and Directorate General of Family Planning (Table 1) use the eRegistry to create client health records across otherwise disjointed silos of the health information system. The eRegistry is configured in the free and open-source DHIS2 tracker. Health workers in the community (family welfare assistants and health assistants) use the eRegistry on a customized Android Tracker app installed on handheld tablets, whereas facility-based users (community health care providers and family welfare visitors) access the eRegistry through a browser on Chromebook (Figure 2). All devices were equipped with SIM cards for prepaid mobile data access. To improve client identification for optimal data continuity in an environment with a few unique identifiers, a palm-based biometric software provided by Element biometrics [18] was made available to the users of the eRegistry. The Element biometrics app was installed on the same device used by the health workers to access the eRegistry. A unique identifier was generated for each client in the biometrics app. Health workers were trained to copy this identifier to the client’s records in the eRegistry. A unique identifier was also generated by the DHIS2 system during the registration of each pregnancy. A demo version of the eRegistry and DHIs is available upon request from the authors.

Paper-based documentation of pregnancies; register books with the number and dates of antenatal, postnatal, and delivery services; and public health reports were maintained along with the eRegistry in both intervention and control health facilities throughout the trial period. Table 1 provides a detailed comparison of the situation before eRegistry implementation in the governmental health system with the control and intervention arms of the trial.

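### Timely antenatal attendance is taken from interviews with women who know whether they received visit reminders, and the blinding described cannot prevent reporting that differs by arm

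*Protocol article*

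**What the plan says.** In Table 2 (Outcomes), the source entry for the first primary outcome is "Postpartum household survey" and nothing else. The second primary outcome is sourced from eRegistry case records. In Table 3, the closely related secondary outcome on a timely first visit lists both eRegistry records and the survey. The survey is a home interview 8-14 days after birth.

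Table 2 names the component with the most direct effect on timely attendance as "Targeted Client Communication via SMS text message: ANC appointment reminders". The Intervention Arm section describes "targeted client communication in the form of SMS text messages to address gaps in the timely attendance of antenatal care visits and facility delivery", and Table 1 ticks this for the intervention arm only. The ethics section says that women are told the purpose and content of the messages.

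On blinding, the article says "The data collectors conducting the postpartum home interviews were blinded to the allocation of individual women". It also blinds the community workers who register women and the researchers who run the final analysis, and says that facility staff could not be blinded. It does not mention the women.

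Two statements leave some role for registry data. The measurement sequence for this outcome in Table 2 includes point-of-care registration, and the text above the table says that outcome data "will be derived from the eRegistry’s client health records and through postpartum home visit interviews". Neither says that registry dates define or verify timeliness.

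**The concern.** The person who supplies the outcome has received, or not received, the component under test. A woman who was sent reminders of routine visits may remember the timing of her visits differently, or be more inclined to describe them as on time, than a woman who was not. An interviewer who does not know her allocation records whatever she says.

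Any difference between arms in reporting error enters the effect estimate directly. It cannot be told apart from a change in attendance, and it falls on the primary outcome that the SMS component is meant to move. The Strengths and Limitations section does not discuss it.

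**Working it through.** **Inputs from the article.** 30 intervention and 29 control facilities (Eligibility Criteria, Cluster Level). Cluster size 77 women and 140 antenatal contacts, control timeliness 20%, target 33%, intracluster correlation 0.1, power above 80% (Sample Size). Two-sided alpha 0.05 is assumed, since the article mentions only 95% CIs.

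**Step 1: the plan's own figure.** Design effect = 1 + (m - 1) × 0.1.
- m = 77: 1 + 76 × 0.1 = 8.6. Effective control sample = 77 × 29 / 8.6 = 259.7. Power for 20% against 33% = 92.5%.
- m = 140: 1 + 139 × 0.1 = 14.9. Effective control sample = 140 × 29 / 14.9 = 272.5. Power = 93.6%.

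The claim of more than 80% is reproduced. The sample size is not at issue here; it supplies the scale.

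**Step 2: false difference from reporting error.** Assume true timeliness of 20% in both arms, that every timely woman reports correctly, and that a share r of untimely women report timely attendance.

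Reported rate = 0.20 + 0.80 × r

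False difference = 0.80 × (r in intervention - r in control)

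The article gives no misreporting rate, so every r below is an assumption.

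| r control | r intervention | Reported rates | False difference | Share of 13 points |
|---|---|---|---|---|
| 5% | 5% | 24% and 24% | 0 points | 0% |
| 5% | 10% | 24% and 28% | 4 points | 4/13 = 31% |
| 5% | 15% | 24% and 32% | 8 points | 8/13 = 62% |
| 10% | 20% | 28% and 36% | 8 points | 62% |

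Only the difference in r matters. The formula is signed: if reminders made intervention women the more accurate reporters, the error would run against the intervention.

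**Step 3: dilution.** If only a share f of untimely intervention women had reminders, and the rest report as controls do, the false difference becomes 0.80 × f × (difference in r). With f = 0.5 (assumption) and a 5-point difference, it is 0.80 × 0.5 × 5 = 2 points.

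**Step 4: against what the trial can detect.** The smallest observed difference that reaches significance is about 1.96 × sqrt(2 × 0.20 × 0.80 × 8.6 / (77 × 29.5)) = 6.8 points for m = 77, and 6.7 points for m = 140. Dividing by 0.80 gives a reporting difference of roughly 8 to 9 points. With no true effect and no over-reporting in control, the chance of a significant result at m = 77 and m = 140 is:
- r = 2%: 7.4% and 7.5%
- r = 5%: 20% and 21%
- r = 10%: 58% and 60%

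**Step 5: which check is safe.** Table 1 gives facility staff access to all records only in the intervention arm, and the Control Arm section says that control users could not see entries made by others. Table 1 also ticks digital client health records for facility staff in the intervention arm only, although the Overview says that both arms enter data at the point of care. Capture in the eRegistry may therefore differ by arm. A check that needs a record to exist can be biased by arm; a comparison of dates on visits that have both a report and a record is less exposed to this.

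**The case against.** The strongest objection is that the mechanism needs visit timing to be recalled, and the questionnaire (Multimedia Appendix 1) is not in the text at hand. Dates may have been copied from a card. This stands: the article does not settle it, and one sentence from the trial team could remove much of the concern.

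The survey is also a defensible source. The eRegistry covers only public primary-level clinics, women use several providers, and entry may be incomplete. This stands too, and is why the survey should remain the primary source.

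Exposure was partial. SMS began in June 2019, the month the survey started and eight months into enrolment, and needed a phone number and consent, with an opt-out. Women interviewed soon after that had spent most of their pregnancy without reminders. This dilutes the effect but does not remove it.

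An article may leave sensitivity analyses to an analysis plan. That is fair as regards their absence. The point rests on what Table 2 does fix: a single source, supplied by women who know whether they were reminded.

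Stronger readings that a reader might infer are not supported:
- That only the interviewer is blinded. Registering workers and analysts are too; they simply have no influence on the woman's answer.
- That registry data are excluded. The measurement sequence and the sentence above Table 2 leave their role unclear.
- That the result will be inflated by 31% or 62% of the target. Those figures are correct arithmetic on assumed rates.
- That a reported visit should count only if a record confirms it. If confirmation fails more often in control, that rule favours the intervention, the same direction as the suspected over-reporting. Agreement between the two versions would then be false reassurance.
- That paper registers could fill the gaps. The article mentions "register books with the number and dates of antenatal, postnatal, and delivery services", but does not say that they carry the study ID, and its data rules keep identifiable data from the researchers.

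**Conclusion.** The concern holds as a risk that the article leaves unaddressed, and it should be dealt with before the allocation is opened. The first primary outcome depends on reports from women who know whether they were sent reminders, and no blinding described in the article prevents reporting that differs by arm.

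The size cannot be determined from the documents. With 20% true timeliness in both arms and full exposure, each 5-point difference in over-reporting among untimely women yields a false 4 points against the 13-point target; a difference of about 8 to 9 points would be enough for significance at the planned size. Both statements rest on assumed reporting rates, and would shrink with partial SMS exposure or documented dates. The documents do not show that such bias occurred, nor fix its direction.

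**What to change.** State whether visit dates in the survey come from recall or from a document such as a card. Then, using the study-ID linkage of eRegistry and survey data already planned under Data Management, pre-specify:

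1. The difference between reported and eRegistry-recorded dates, by arm, for public-clinic visits that have both. Fix the matching rule in advance and use it in both arms; a tight date window would itself hide discrepancies.
2. A sensitivity analysis of the first primary outcome that replaces the reported date with the recorded date for those matched visits, and keeps the survey report for all other visits, including private and NGO visits.
3. The share of reported public-clinic visits with an eRegistry match, by arm.

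Unmatched visits should not be counted as untimely. No paper-register look-ups are needed, and there should be no rule that both versions must agree. If reporting error differs by arm, the conclusion on attendance should be qualified.

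The cost is a little more analysis on data that will be linked anyway. The limits are that matched visits are a selected subset, and that a reported visit that never took place has no record to compare with. This is a check on the survey, not a replacement for it.
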